**Surveys**

**Baseline:** All participants complete a self-administered survey on an online survey platform (Wen Juan Xing, https://www.wjx.cn) at enrolment. The baseline survey includes questions on socio-demographic characteristics, sexual behaviors, past HIV/syphilis testing and treatment, and attitude towards syphilis self-testing.

**Follow-up surveys:** Participants in the three arms of the study will complete a brief online survey at three-monthly intervals. The follow up surveys collects information on the number, time, location, reasons for, and results of syphilis tests (including self-tests) and other STI tests at clinics and community sites, and sexual risk behaviors in the past three months. Participants in the two self-testing arms are also asked about the number of self-test kits they used to test their sexual partner(s) or if they gave any kits to someone else to test. At the last follow-up, participants will be asked to get STD (HIV, syphilis, chlamydia, and gonorrhea) screening test in their nearby clinic. The testing fee will be redeemed by an upload of the test results. Participants will be provided with 30 RMB (equal to 4 US Dollars) for their time to complete each follow-up survey.

**Statistical methods**

***Sample size***

According to our initial pilot study (***Supplementary material***), the proportion of individuals who undertook a syphilis test was 0.36 (95% confidence interval: 0.22 – 0.52) at the one-month follow-up in the control arm. This increased to 0.74 (95% confidence interval: 0.61 – 0.81) in the self-testing arm. On this basis, for the primary outcome with 80% statistical power and type I error probability of 0.05, we conservatively estimate a sample size of 29 per arm (including 20% loss to follow up [25]) for this study. According to our previous experience on using the crowdsourced HIV self-testing intervention in increasing HIV testing among MSM (the proportion was 0.85 [25]), we estimate a sample size of 148 for each arm to achieve 80% power to detect a difference between the crowdsourced lottery incentivized self-testing arm and standard syphilis self-testing arm. Finally, a total of 444 (148 per arm) will be enrolled in this trial.

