**Study design**

This is a non-blinded, open-label, parallel RCT with individuals randomized in a 1:1:1 ratio to three study arms: control arm (standard of care); standard syphilis self-testing arm; and lottery incentivized syphilis self-testing arm. Control arm participants will receive information on self-referral pathways for free facility-based syphilis testing. Both self-testing arms will be offered to access syphilis self-test kits for free at monthly intervals. Participants in each arm will be followed-up for six months (Figure 1). The study hypothesis had been tested in a pilot study, completed in October 2019, which examined the feasibility of implementing the self-testing and crowdsourced lottery incentivized syphilis self-testing model among 145 Chinese MSM. The pilot study showed that both standard self-testing arm (0.74) and lottery incentivized arm (0.70) increased the frequency of syphilis testing more than the control arm (0.36). Preliminary data from this pilot study was used to inform this definitive trial design. Preliminary results are available on the supplement materials. The definitive trial, outlined in the current trial protocol, has begun in December 2019, and is expected to be completed in July 2020.

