**Outcomes Measures**

The primary outcome is the proportion of participants who tested for syphilis during the trial. Syphilis tests may be either at a clinic or via self-test. This will be verified in all participants using photo-verification. We will additionally look at the incremental benefit of the lottery incentive efficacy in promoting syphilis, number of newly identified syphilis infections, the linkage to syphilis clinical care after self-testing, the proportion of HIV and other STIs (chlamydia, gonorrhea) tests among the participants who use self-testing and cost-effectiveness of syphilis self-testing in promoting uptake of syphilis testing among Chinese MSM.

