The major challenge of this study is to retrieve validated testing proof to verify self-testing results. Our previous study reported that 47% of men submitted proof of syphilis self-testing with 20 RMB (about 3 US dollar) cash incentive [[18](#_ENREF_18)]. This was a cross sectional survey, and people are not always able to find the required proof, especially for those who tested a long time ago. Furthermore, we cannot guarantee that submitted photographic proofs truly belongs to the patient. We previously found that more than 30% of men would submit a proof of testing even if no incentive was offered in an HIV self-testing study [[25](#_ENREF_25)]. To increase the retrieval rate, we will provide a small cash incentive (5 RMB) to reimburse their submission of self-testing results or other testing proof materials. To link self-test kits with the user, we will code each self-testing package and direct them to take a photo of the used strip with the background of the package, which has been successfully tested in our pilot trial.

Another potential limitation of this study is the possibility of contamination between arms. We cannot prevent participants from the control arm to purchase syphilis self-testing kits for use through online e-market which we have been previously found in some MSM in China [[18](#_ENREF_18)]. To mitigate this, we will record the participants’ testing method in each group and if necessary adjust for this in the data analysis. The six-month duration of follow-up also limits the ability of the study to assess the long-term effect of the intervention on syphilis incidence.

Findings from this proposed study will be used to inform the design of a new syphilis self-testing model, which will be implemented alongside the traditional facility-based testing service to increase syphilis screening among MSM in China. We anticipate that the model will increase early syphilis diagnosis and enhance syphilis continuum of care and treatment for MSM, and ultimately reduce the spread of syphilis and HIV transmission among MSM and other individuals within their sexual networks in China.

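### The 80% power claimed at 148 per arm for lottery versus standard self-testing is not established on the photo-verified syphilis-testing endpoint

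*Protocol*

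**What the plan says.** **Endpoint.** Under Outcomes Measures, the primary outcome is the proportion of participants tested for syphilis during the trial, by self-test or at a clinic. The section adds: "This will be verified in all participants using photo-verification". Data collection says the same for both routes: a photo of the used kit, or of the facility's test report.

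**Sizing.** The Sample size section works "with 80% statistical power and type I error probability of 0.05". For the standard self-testing arm it uses the pilot: "This increased to 0.74 (95% confidence interval: 0.61 – 0.81) in the self-testing arm". Standard self-testing against control needs only 29 per arm, including 20% loss to follow-up. The trial's size comes from the lottery-versus-standard contrast: "in increasing HIV testing among MSM (the proportion was 0.85 [25]), we estimate a sample size of 148 for each arm". Sidedness, the standard-arm rate used for this contrast, and how the 0.85 and the pilot rates were ascertained are not stated.

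**Pilot.** Study design reports that "both standard self-testing arm (0.74) and lottery incentivized arm (0.70) increased the frequency of syphilis testing more than the control arm (0.36").

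**Proof of testing.** The Discussion names obtaining valid proof as the study's main difficulty. It reports that "47% of men submitted proof of syphilis self-testing with 20 RMB (about 3 US dollar) cash incentive" in an earlier cross-sectional survey. From reference 25, the source of the 0.85, it reports that "more than 30% of men would submit a proof of testing even if no incentive was offered in an HIV self-testing study". This trial pays 5 RMB per uploaded photo in all arms. In the lottery arm the draw also requires a photo (Table 1).

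**The concern.** The quantity that was sized and the quantity that will be counted are not shown to be the same. The 0.85 concerns HIV testing, comes from another study, and has no stated method of ascertainment. The trial counts a syphilis test only once a photo has been accepted. The 20% allowance is for loss to follow-up, which is a different loss: a man can answer the survey, have tested, and still send no photo.

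This contrast alone drives the enrolment of 444. If verification is incomplete to a similar degree in both arms, both proportions shrink and so does their difference. A null lottery result could then be read as showing no added benefit when the trial had little chance of showing one. If verification differs between arms, a positive result could partly reflect who uploads photos rather than who tests.

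**Working it through.** **Inputs.** Alpha 0.05 (two-sided assumed), power 80%, 20% loss, control 0.36, standard 0.74 and lottery 0.85 (Sample size); pilot lottery rate 0.70 (Study design). The 20% loss is stated for the 29 per arm and is assumed to apply to the 148 as well.

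**Step 1: reproduce the plan.** Unpooled two-proportion formula:

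n = (1.960 + 0.842)² × [p1(1−p1) + p2(1−p2)] / (p1−p2)², then divide by 0.8. The first factor is 7.849.

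- 0.36 vs 0.74: 7.849 × 0.4228 / 0.1444 = 22.98, so 23; 23/0.8 = 28.75, so 29. This matches the plan.
- 0.70 vs 0.85: 7.849 × 0.3375 / 0.0225 = 117.7, so 118; 118/0.8 = 147.5, so 148. This matches the plan.
- 0.74 vs 0.85: 7.849 × 0.3199 / 0.0121 = 207.5, so 208; 208/0.8 = 260. This does not match.

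Pooled, continuity-corrected, arcsine and one-sided variants of 0.74 vs 0.85 do not give 148 either: they need 164 to 229 before loss and 205 to 287 after. So 148 rests on 0.70 as the comparator, and in the pilot 0.70 is the lottery arm's rate, not the standard arm's.

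**Step 2: power with every test verified.** Pooled-null normal approximation, two-sided 0.05:

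power = Φ{ [d√n − 1.960 √(2p̄(1−p̄))] / √(p1(1−p1) + p2(1−p2)) }, with d the difference and p̄ the mean of the two proportions.

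| Rates | 118 evaluable per arm | 148 per arm |
|---|---|---|
| 0.70 vs 0.85 | 79% | 88% |
| 0.74 vs 0.85 | 55% | 65% |

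**Step 3: equal verification v in both arms.** This is an assumption; the Protocol gives no v for this trial. The rates become v·p1 and v·p2. At v = 0.8, 0.70 vs 0.85 becomes 0.56 vs 0.68, so d = 0.12 and, with n = 118, (1.304 − 1.960 × 0.686) / 0.681 = −0.06, which gives 48%.

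| v | 0.70 vs 0.85: 118 / 148 | 0.74 vs 0.85: 118 / 148 |
|---|---|---|
| 0.9 | 62% / 72% | 39% / 47% |
| 0.8 | 48% / 57% | 29% / 35% |
| 0.7 | 37% / 44% | 22% / 27% |

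**Step 4: unequal verification.** With 0.70 vs 0.85 and 118 evaluable:

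| v standard / v lottery | Verified rates | Power |
|---|---|---|
| 0.8 / 0.8 | 0.56 vs 0.68 | 48% |
| 0.8 / 0.85 | 0.56 vs 0.7225 | 74% |
| 0.8 / 0.9 | 0.56 vs 0.765 | 92% |

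In the last row the difference is 0.765 − 0.56 = 0.205. It splits into 0.8 × (0.85 − 0.70) = 0.12 from testing and 0.85 × (0.9 − 0.8) = 0.085 from uploading.

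**Step 5: if the pilot rates are already photo-verified.** Only the 0.85 would then need discounting. At v = 0.9 it becomes 0.765, and the difference falls to 0.065 against 0.70 or 0.025 against 0.74.

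**Step 6: standard self-testing vs control.** Even at v = 0.47 the rates are 0.169 vs 0.348, with 88% power at 118 per arm. The problem is confined to the lottery contrast.

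**The case against.** The best defence is that the Protocol does not show verification will be poor. Several points in it stand.

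- A reader might infer that the 0.85 was self-reported, because only about 30% of men in that study sent proof. The text does not support this. It says more than 30% would do so without an incentive, which is a lower bound with no stated denominator, and nowhere does it say how the 0.85 was measured.
- A reader might also carry the 47% over as this trial's verification rate, which at v = 0.47 would give 20% power (0.70 vs 0.85, 118 evaluable). The Discussion itself warns that this was a cross-sectional survey and that men who tested long ago may not find proof. Here photos are sent prospectively, kits are coded and photographed with the used strip (a method tried in the pilot), and the final clinic test fee is refunded on upload of results. Verification may well be higher.
- Equal verification is only an assumption. The draw requires a photo, so lottery-arm men have an extra reason to upload, and Step 4 shows that power can then exceed 80%. It is therefore not established that power must be far below 80%.
- The pilot rates may already be photo-verified, in which case scaling them again would discount them twice.

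None of this restores the stated 80%. Power gained through unequal uploading does not measure testing. Verified pilot rates would leave the 0.85 alone to be discounted, which shrinks the contrast further. And the stated 0.74 gives 55% to 65% before any verification loss.

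**Conclusion.** The concern holds in this form: the 80% power at 148 per arm for lottery versus standard self-testing is not established for the trial's own endpoint. The lottery rate is an HIV-testing proportion not shown to be photo-verified, no allowance is made for unproven tests, and the figure reproduces only with a comparator that differs from the stated standard-arm rate.

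How far true power departs from 80% cannot be fixed from the Protocol. The Step 3 figures rest on equal verification, two-sided testing and 20% loss, and are a range rather than a forecast. Of the results, only the 55% (118 evaluable) to 65% (148) for 0.74 vs 0.85 is free of any assumption about incomplete verification, though it still takes the 0.85 at face value. The comparison of standard self-testing with control is not threatened.

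**What to change.** In the Sample size section of the Protocol:

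1. State how the 0.85 and each pilot rate were ascertained (reported or photo-verified), and that the 0.85 is an HIV-testing figure.
2. State which standard-arm rate was used for the lottery contrast, and reconcile it with the 0.74.
3. Apply an explicit verification rate, but only to rates that are not already photo-verified.
4. Show power at 148 per arm, with and without the 20% loss, over a range of equal and unequal verification.
5. Withdraw the unqualified 80% claim for this contrast and report the contrast as an estimate with a confidence interval.

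The cost is a rewritten paragraph and a less favourable stated power for the lottery comparison. No added enrolment or change of design is proposed.

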#### *Analysis plan*

Data will be retrieved from the online survey platform. De-identified datasets and codebook will be stored for statistical analysis. The syphilis testing proportion in each arm (control, standard self-testing, and lottery incentivized self-testing) will be assessed using an intention-to-treat analysis during the follow-up period, excluding confirmatory tests after a reactive self-test.

The effects of the intervention will be measured by comparing the differences in proportions of men who take syphilis testing during two rounds of follow up by using generalized estimating equation (GEE) model. We will use the chi-square test to compare differences in the proportion of linkage to syphilis clinical care, have HIV and other STI (chlamydia, gonorrhea) testing performed, and have condomless sex events with different partners within six months of randomization across three groups and use post-host test to check the significance of differences between each of the two groups.

We will estimate the total and incremental unit costs for each arm. All costs will be identified as start-up costs, fixed costs and variable costs. Start-up costs are incurred during the process of creating this study (e.g. survey platform coordination). Fixed costs are costs that do not change with an increase or decrease in the number of people served during the trial period (e.g. administration, office equipment). Variable costs are expenses that vary with the number of participants served (e.g. recruitment, supplies, postage fee). We will first calculate the total cost for each group, then divided these costs by the number of men tested and the number of newly identified syphilis cases detected in each study arm to obtain the incremental unit costs. In addition, we will build a decision tree model using a healthcare provider perspective to estimate the incremental cost for per additional person tested and case identified for each intervention will be calculated. Univariate, multivariate and probabilistic sensitivity analyses will be conducted to test the robustness of our results.

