***Missing data plan***

We anticipate the loss to follow-up will be less than 20% for the first three months. If outcome measures are missing less than 11% of participants, then the primary analysis will use a complete-case approach. If the outcome measures are missing for 11% to <20% of participants, then a sensitivity analysis using multiple imputation will be used to compute the missing outcome of the three arms.

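### The intention-to-treat, photo-verified outcome and the complete-case rule imply different primary denominators, and at the standard arm's own pilot rate 148 per arm misses 80% power for lottery versus standard self-testing under either

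*Protocol*

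**What the plan says.** All places are in the protocol.

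- **Outcomes Measures:** the primary outcome is the proportion tested during the trial, at a clinic or by self-test. "This will be verified in all participants using photo-verification". Data collection repeats that self-tests and facility tests are both established from a photo.
- **Analysis plan:** the testing proportion in each arm "will be assessed using an intention-to-treat analysis during the follow-up period". The effect is estimated by GEE over two follow-up rounds, with data taken from the survey platform.
- **Missing data plan:** if fewer than 11% of outcomes are missing, "then the primary analysis will use a complete-case approach". From 11% to below 20%, multiple imputation is a sensitivity analysis and no primary method is named. Nothing is given for 20% or more. Loss is expected to stay below 20% over the first three months.
- **Sample size:** in the control arm of the pilot "the proportion of individuals who undertook a syphilis test was 0.36", against 0.74 with self-testing. With "type I error probability of 0.05" and 80% power this gives 29 per arm including 20% loss. For lottery versus standard self-testing, with 0.85 taken from an earlier crowdsourced HIV self-testing study, "we estimate a sample size of 148 for each arm to achieve 80% power to detect a difference". The 20% is not repeated for this figure, and the comparator rate is not stated.
- **Study design:** the pilot rates are given as "both standard self-testing arm (0.74) and lottery incentivized arm (0.70".

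**The concern.** Dividing a sample size by 0.80 is right when lost men drop out of numerator and denominator alike. It does not fit an analysis that keeps every randomised man and recognises a test only by photo. There, a man who uploaded before he was lost is an observed success, and a man who never uploaded may be counted as a failure. Loss then lowers both proportions and the gap between them, and a larger enrolment by 1/0.80 does not offset that.

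The protocol contains both approaches and no rule for choosing between them. If complete-case is applied by survey completion, it can also delete men whose verified test is already on file. In an open-label trial, leaving the primary denominator open until data are in hand invites a discretionary choice. The comparison affected is lottery versus standard self-testing, which sets the size of the whole trial.

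**Working it through.** **Inputs.** Alpha 0.05 (sidedness not stated; two-sided is used because it reproduces the 29), power 80%, pilot rates 0.36 (control), 0.74 (standard self-testing) and 0.70 (lottery), assumed lottery rate 0.85, loss 20%, 148 per arm.

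**1. The plan's 29.** Unpooled formula: n = (1.960 + 0.842)² × [p1(1−p1) + p2(1−p2)] / (p2−p1)², where the squared term is 7.849.
- 0.36 v 0.74: 7.849 × 0.4228 / 0.1444 = 22.98, so 23. 23/0.80 = 28.75, so 29. This matches.

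**2. The plan's 148, same method.**
- 0.74 v 0.85: 7.849 × 0.3199 / 0.0121 = 207.5, so 208. 208/0.80 = 260. This does not match. Pooled variance gives 211 and 264. Even one-sided, 164 are needed before any loss.
- 0.70 v 0.85: 7.849 × 0.3375 / 0.0225 = 117.7, so 118. 118/0.80 = 147.5, so 148. This matches.

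Of the pilot rates for the two self-testing arms, only 0.70 returns 148, and 0.70 is the lottery arm's rate. The match also shows that the 148 carries the 20% allowance and treats lost men as removed.

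**3. What the stated rules do with lost men.**

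| Missing outcomes | Primary analysis stated | Do men leave the denominator? |
|---|---|---|
| below 11% | complete-case | yes |
| 11% to below 20% | none named; imputation as sensitivity | not stated |
| 20% or more | none | not stated |

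So at the 20% loss used for sizing, no written rule removes men.

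**4. Power at 148 per arm with 20% loss.** Exact power of the two-sided Pearson chi-square test. Assume equal loss in both arms, unrelated to testing, and let f be the share of lost testers who uploaded a photo before loss. With all 148 kept and no photo counted as not tested, each rate is multiplied by 0.8 + 0.2f. The documents do not give f.

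| f | rates from 0.74 v 0.85 | power | rates from 0.70 v 0.85 | power |
|---|---|---|---|---|
| 0 | 0.592 v 0.680 | 35% | 0.560 v 0.680 | 57% |
| 0.25 | 0.629 v 0.723 | 41% | 0.595 v 0.723 | 64% |
| 0.50 | 0.666 v 0.765 | 47% | 0.630 v 0.765 | 72% |
| 0.75 | 0.703 v 0.808 | 55% | 0.665 v 0.808 | 80% |
| 1 (same as no loss) | 0.740 v 0.850 | 66% | 0.700 v 0.850 | 88% |

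If the 20% are removed instead (148 × 0.8 = 118 per arm), power is 56% with 0.74 and 80% with 0.70. At 10% loss, where complete-case is the stated rule (148 × 0.9 = 133 per arm), 0.74 v 0.85 gives about 61%. A normal approximation agrees within about one percentage point.

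**5. Verified testers that complete-case could drop.** At the 11% limit, if missing is judged by survey completion and every lost tester had already uploaded: 0.11 × 148 × 0.74 = 12.0 in the standard arm and 0.11 × 148 × 0.36 = 5.9 in control. These are upper bounds.

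**6. Standard self-testing versus control.** With 20% loss all counted as not tested: 0.8 × 0.36 = 0.288 v 0.8 × 0.74 = 0.592. Power at 148 per arm exceeds 99.9%.

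**The case against.** The strongest reply is that no section says a lost man without a photo is untested. Intention-to-treat fixes analysis by assigned arm; counting missing as failure is a separate convention. The Missing data plan assumes that outcomes can be missing, and the surveys ask about tests, so a non-responder can be missing. Complete-case analysis is exactly what division by 0.80 supposes, and detailed scoring may sit in a SAP that is not shown. All of that stands. A reader might infer that the plan scores lost men as untested by rule, and that its power is therefore 57%. The documents do not support that: it is one reading of the outcome and intention-to-treat statements.

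A reader might also infer that about 22 verified testers would be discarded in the standard arm (0.20 × 148 × 0.74 = 21.9). That does not hold either, because complete-case is prescribed only below 11%, where the bound is about 12. If missing simply means no photo, nobody with a verified test is dropped.

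Three further limits stand. With 0.70 as the base, 57% to 88% straddles 80%, so loss handling alone does not prove a shortfall. The pilot rates may already count non-uploaders as untested, in which case multiplying by 0.8 counts loss twice; the pilot supplement is not at hand. And the planned GEE uses two rounds, so a man lost after the first can still contribute, which a single chi-square test ignores.

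The reply does not close the gap between an 11% ceiling for complete-case and a 20% loss in the sizing. Nor does it touch the shortfall at 0.74, which appears even with no loss.

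**Conclusion.** The point holds as a conflict between written rules together with an overstated power. The photo-verified, intention-to-treat outcome and the complete-case rule give different primary denominators, and the protocol does not say which governs. The 148 per arm assumes that lost men are removed at a loss level where no stated rule removes them.

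With the standard arm's own 0.74 against 0.85, 148 per arm does not reach 80% under either denominator: about 66% with no loss, about 56% with 20% removed, and about 35% to 66% with 20% lost and no photo counted as not tested. The last range depends on the unknown share who upload before loss. All figures assume a two-sided 5% test, equal loss across arms unrelated to testing, and a single comparison of proportions. If 0.70 could be justified for the standard arm, they would be 88%, 80% and 57% to 88%.

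The shortfall is confined to lottery versus standard self-testing. It should not be read as a weakness in standard self-testing versus control, where power stays above 99.9%.

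**What to change.** **Analysis plan and Missing data plan.** State that the primary denominator is all randomised men in each arm. A verified photo within the follow-up period counts as tested even if the man is later lost. No photo counts as not verified as tested. Move the complete-case and multiple-imputation analyses to sensitivity, whatever the percentage missing.

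**Sample size.** Give the comparator rate and the loss assumption behind the 148. Replace the flat 80% for lottery versus standard self-testing with the power under the rule above at 0.74 versus 0.85: about 35% to 66% at 20% loss, with the assumed share uploading before loss, alongside about 66% with no loss and, for the complete-case sensitivity analysis, about 56%. Quote the 0.70-based 57% to 88% only if 0.70 is justified for the standard arm.

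**Cost.** Protocol wording and a less favourable stated power; no extra men and no new data. The rule counts a real but unphotographed test as a failure, and the lottery draw gives that arm an added reason to upload. A sensitivity analysis that uses the survey reports of testing should therefore accompany it.
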